### Other Measures

*Stress* will be measured using salivary cortisol concentrations. Saliva samples (collected immediately on waking on testing days and immediately pre- and post-testing) will be centrifuged and frozen at −80° Celsius and concentrations measured using the ELISA kit Abcam, ab154996. *Mood* will be assessed using the Positive and Negative Affect Scale (PANAS; Crawford and Henry, 2004). *Alertness* will be measured using a simple visual analog scale (VAS; Monk, 1989). *Sleepiness* will be measured using the Karolinska Sleepiness Questionnaire (Putilov and Donskaya, 2013). *Blood glucose* will be collected continuously using an Abbott FreeStyle Libre system (Abbott Scandinavia AB, Abbott Diabetes Care, Solna), which records glucose concentration in the interstitial fluid every minute.

### Sample Size

Several studies (Hyodo et al., 2012; Endo et al., 2013; Byun et al., 2014; Bediz et al., 2016; Carter et al., 2018; Kujach et al., 2018; Ichinose et al., 2020) on the acute effects of light, moderate, and intense physical activity on post-exercise cerebral blood flow have been performed on similar, but not identical, designs and interventions as in our study, but have used comparable populations. Data from these studies were used to recalculate effect sizes using G*Power software (Franz Faul, Universität Kiel, Germany, v 3.1.9.2). Results showed effect sizes between 0.9 and 2.4, rendering a minimum sample size of between 6 and 13 individuals with an *α* = 0.05 and *β* = 0.8 assuming a two-tailed test. We chose to match our sample size to the largest found among the reviewed studies, namely 13 subjects.

### Data Analysis

To answer our primary research question, linear mixed-effects models with subject as the random effect will be used to assess within condition differences in the changes in cerebral blood flow (oxy-Hb) between pre- and post-tests correcting for multiple comparisons from estimation over many channels, using Benjamini–Hochberg. Time and condition interactions will be used to estimate differences between conditions. Baseline arterial stiffness will be assessed as a moderator in the models. Linear mixed models will also be used to assess secondary outcomes, to investigate within-person changes from pre- to post-test, and between conditions. Stata version 15 (StataCorp, College Station, TX, USA) and NIRSToolboxAnalyzer (Santosa et al., 2018) will be used for statistical analyses.

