## Materials and Methods

### Design

A crossover randomized 3-condition experimental trial will be carried out with a target sample size of 13 participants. All study procedures will occur at the Swedish School of Sport and Health Sciences (GIH) in Stockholm, Sweden. Participants will be recruited from the general Swedish population using social media, GIH’s homepage, and newspaper advertisements. As well, through the Swedish Armed Forces’ personnel magazine and word of mouth. Participants will initially attend a familiarization session for the collection of demographic data, fitness testing, and acquaintance with experimental procedures. Each participant will undergo 3-h experimental conditions in random order, with a minimum washout period of 4 days between each of the three visits (Bell et al., 2018). Physical activity, sleep, and glucose levels will be measured for the 24 h before each condition. A computer-generated randomization schedule will be created before study commencement, and participants will be randomized to a condition order at the end of the familiarization session. This trial obtained ethical approval by the Swedish Ethical Review Authority, Stockholm, Sweden (Dnr 2019-00998). Trial registration for experimental studies of this nature is not required but is increasingly being recognized as good practice (English et al., 2020). Therefore, we registered this trial at www.clinicaltrials.gov (NCT04137211) on October 23, 2019, after recruitment began on May 13, 2019.

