#### Cognitive Performance

Cognitive performance in working memory will be assessed using a computerized n-back test (Kirchner, 1958), consisting of the 1-, 2-, and 3-back tests administered simultaneously with fNIRS measures. We will use a computerized, numerical version of the n-back, whereby participants will be required to indicate (*via* a keypress within 2 s from stimulus onset) whether the digit presented on the screen was the same as the digit presented 1 stimulus previously (1-back), 2 stimuli previously (2-back), or 3 stimuli previously (3-back). Each digit will be presented for 1.5 s at an interstimulus interval of 500 ms. The n-back tests were created using E-Prime 2.0 (Psychology Software Tools). To reduce practice effects, participants will perform practice tests before data collection on each experimental day. The outcome variables for cognitive performance will include average reaction time (ms) and accuracy (average number of correct responses) for each test across two blocks of 20 digit sequences (1-back) or four blocks of 20 digit sequences (2- and 3-back).

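### The primary mixed model omits the visit level: if values from one visit are correlated beyond the subject effect, the condition comparison loses power

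*Protocol article*

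**What the plan says.** The Data Analysis section fixes the random part of the primary model as "linear mixed-effects models with subject as the random effect". For the comparison between conditions it adds: "Time and condition interactions will be used to estimate differences between conditions". Only subject is named as a random effect.

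The Design section describes a three-condition crossover "with a target sample size of 13 participants", and says: "Each participant will undergo 3-h experimental conditions in random order". Visits are at least 4 days apart. The article gives neither the number of condition orders nor a method of balancing them. The Outcome Measures section places one measurement directly before and one directly after each condition, which makes six values per participant for each channel and load contrast.

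The Cerebral Blood Flow section defines the primary variables as oxy-Hb differences between task loads (2-back against 1-back, 3-back against 1-back) within a session. The Cognitive Performance section states: "To reduce practice effects, participants will perform practice tests before data collection on each experimental day".

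**The concern.** A time-by-condition interaction needs pre and post as separate rows. Those rows are nested in visits, and visits in participants. With a subject intercept alone, the model assumes that pre and post from the same day are no more alike than values from different days. Yet the plan treats day-to-day state as worth controlling: it monitors sleep, activity, diet and glucose over the 24 hours before each visit.

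The quantity of interest, the difference between conditions in pre-post change, is a within-visit contrast, so a visit's overall level drops out of the estimate. In the subject-only model that level does not drop out of the residual variance, so the standard error is too large whenever visits vary. A trial of 13 people that also corrects over many channels has little power to give away.

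A secondary issue is order. Thirteen is not a multiple of 3 or 6, so condition orders cannot be exactly balanced, and the named model terms do not include visit number.

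**Working it through.** **Inputs.** From the protocol article: 13 participants, 3 visits, 2 times, two-sided alpha 0.05, smallest planning effect size 0.9. The Sample Size section writes "with an *α* = 0.05 and *β* = 0.8 assuming a two-tailed test"; 0.8 is read here as power. The ratio L = visit variance / residual variance is in no document and is varied as an assumption.

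**The plan's own figure.** The Sample Size section reports "effect sizes between 0.9 and 2.4, rendering a minimum sample size of between 6 and 13 individuals". A two-sided paired t-test at d = 0.9 needs 12 participants (power 0.810 at 12, 0.845 at 13), and d = 0.85 needs exactly 13. At d = 2.4 it needs 4, against the stated 6. The chosen 13 is therefore consistent with a paired comparison at the low end of the range.

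**Degrees of freedom**, with 13 × 3 × 2 = 78 values:
- Subject-only residual: 78 − 1 − 5 (fixed cells) − 12 (subjects) = 60.
- Visit-level part (subject × condition): 12 × 2 = 24, expected mean square σ² + 2σv².
- Within-visit part (subject × time, and subject × time × condition): 12 + 24 = 36, expected mean square σ².

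**Expected residual variance of the subject-only model:**

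[24(σ² + 2σv²) + 36σ²] / 60 = σ² + 0.8σv²

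**Standard error.** The difference in pre-post change between two conditions has true variance 4σ²/13. The subject-only model estimates 4(σ² + 0.8σv²)/13. The ratio of standard errors is sqrt(1 + 0.8L).

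**Consequences at 13 participants** (simulation on this layout, two-sided 5%; d is the mean difference in change divided by its between-participant SD, 2σ):

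| L | SE ratio | Type I error | Power at d = 0.9 |
|---|---|---|---|
| 0 | 1.00 | 0.050 | 0.89 |
| 0.25 | 1.10 | 0.032 | 0.85 |
| 0.5 | 1.18 | 0.021 | 0.80 |
| 1 | 1.34 | 0.010 | 0.71 |
| 2 | 1.61 | 0.003 | 0.52 |

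With a visit-within-subject intercept, type I error is about 0.05 and power at d = 0.9 about 0.88 at every L. For an effect sized so that the correct analysis has 80% power, the subject-only model has about 0.71 at L = 0.5 and 0.59 at L = 1.

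**Order.** For one participant in random order, the difference in position between two conditions is ±1 in 4 of the 6 orders and ±2 in the other 2. Its variance is (4 × 1 + 2 × 4)/6 = 2. Under unrestricted randomisation, the difference in mean visit number over 13 participants has mean zero and SD sqrt(2/13) = 0.39 visits. If the six orders are used twice each (12 participants), the thirteenth leaves 1/13 to 2/13, or 0.08 to 0.15 visits. This biases the condition contrast only through an order effect on the pre-post change. A shift common to pre and post of one visit cancels.

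**The case against.** **The premise may not hold.** No visit variance is given, and at L = 0 the stated model is correct. The primary variable is already a difference between task loads within a session, so an additive shift shared by the whole session is removed before the model is fitted. This stands. It is why L must be shown as a range and why small values are plausible. Effects that scale the signal, such as those of optode placement, would not be removed this way.

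**The model may be on change scores.** The same section also speaks of changes between pre and post. With one change per visit, a subject effect is enough. However, a time-by-condition interaction cannot be fitted to change scores, so the text as written points to separate rows. The sentence should be made unambiguous.

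**Stronger readings that a reader might infer.**
- *The standard errors are certainly wrong.* They are wrong only if there is variance that the model omits.
- *The trial risks false positives.* Visit variance makes the condition comparison conservative. Within-condition tests can exceed 5% (about 6 to 8% in simulation), but this needs a different assumption: participants differ in their pre-post trend and visits do not vary.
- *Order effects cannot cancel.* Exact balance is impossible, but imbalance averages zero under randomisation and is small if orders are nearly balanced. The article does not say that randomisation is unrestricted.
- *The plan has left out a period term.* The article is condensed, and its silence on visit number does not show that the full plan lacks one.
- *The practice-test sentence shows that practice will bias the comparison.* That sentence describes a mitigation, and practice that shifts pre and post alike cancels.

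**Conclusion.** The point holds as a conditional weakness of a model that the article states explicitly. With subject as the only random effect and pre and post as separate rows, any positive visit variance inflates the standard error of the condition comparison by sqrt(1 + 0.8L). At assumed ratios of 0.5 and 1 this is 18% and 34%. Relative to a model with the visit level, power at d = 0.9 then falls from about 0.88 to 0.80 and 0.71. At the first of these the trial still has its nominal 80% at its smallest planning effect; at the second it does not. The figures assume complete data and no participant-specific trends.

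The cost is mainly the chance of missing a real effect. It also bears on the hypothesis that cerebral blood flow will not rise after uninterrupted sitting, because an oversized standard error makes a null result there easier to obtain. The order issue is minor and supports an inexpensive extra term, not a criticism of validity.

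**What to change.** Do one of the following in the Data Analysis section:
- add a random intercept for visit within subject to the pre/post model; or
- analyse one pre-post change per visit, with condition as a fixed effect and subject as the random effect.

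With complete data both give the same condition estimates free of visit variance. The second uses 24 error degrees of freedom instead of 36 (39 changes − 1 − 12 − 2 = 24) and also allows participants to differ in their trend. Estimate by REML with small-sample degrees of freedom such as Kenward-Roger.

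As an addition, include visit number (1, 2, 3) as a categorical fixed effect, with its interaction with time if pre and post are both modelled. This costs 2 degrees of freedom on change scores, or 4 in the pre/post model. State how many condition orders are used and how they are balanced.

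The change is to wording only. It needs no new data and leaves the sample size at 13. If visit variance proves to be zero, almost nothing is lost: power at d = 0.9 is 0.88 instead of 0.89.

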1In middle-aged adults, what are the acute (immediate) effects of uninterrupted sitting and frequent, short activity breaks during 3 h of sitting on cerebral blood flow in the prefrontal cortex?Our *secondary* research questions are:2In middle-aged adults, what are the acute (immediate) effects of uninterrupted sitting and frequent short activity breaks during 3 h of sitting on:(a)Cognitive performance?(b)Psychological factors (stress, mood, alertness, and sleepiness)?(c)Post-prandial blood glucose?3Does vascular health (arterial stiffness) attenuate the effects of activity breaks on cerebral blood flow?Based on previous research, we hypothesize that:(a)Changes in neural activity-related prefrontal cortex cerebral blood flow (hereafter termed cerebral blood flow) from pre-test to post-test will be greater following the conditions with frequent, short activity breaks compared with the uninterrupted sitting condition;(b)Cerebral blood flow will be greater post-intervention compared to pre-intervention for the frequent, short activity breaks conditions, but not for the uninterrupted sitting condition;(c)Improvements in cognitive performance will be larger in magnitude in the frequent, short activity breaks conditions compared with the uninterrupted sitting condition;(d)The frequent, short activity break conditions will lead to improvements in psychological factors, compared with the uninterrupted sitting condition;(e)Glucose levels will not differ between the conditions;(f)Arterial stiffness will temporarily decrease immediately after the frequent, short activity break conditions (compared to pre-test levels), but will not change after the uninterrupted sitting condition; and(g)Arterial stiffness will moderate the effect of frequent, short activity breaks on cerebral blood flow, such that participants with lower arterial stiffness at baseline will have greater cerebral blood flow after the frequent, short activity break conditions compared with participants with higher arterial stiffness.

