### Pre-experimental Day Monitoring

To standardize the 24 h before each test day, participants will be advised to abstain from any physical activity and alcohol intake and will be asked to record details about their physical activity and sleep in a standardized diary. Participants will also wear activity monitors during this period to collect objective data about physical activity (hip-worn actigraph GT3X+ and activPAL micro) and sleep (wrist-worn actigraph GT3X+). Physical activity variables from the actigraph will include total physical activity and percentages of wear time spent in sedentary, light, and moderate-to-vigorous physical activity, according to standardized cut-points (Sasaki et al., 2011; Aguilar-Farias et al., 2014). Physical activity variables from the activPAL micro monitor will include time spent sitting including in prolonged bouts (>20 min), number of breaks from sitting each hour and time spent standing, stepping, and intense stepping. During night time, participants will wear the actigraph GT3X+ on the non-dominant wrist (Cellini et al., 2013). Using the existing Cole-Kripke algorithm (Cole et al., 1992), the following key aspects of sleep will be calculated: time to sleep onset, sleep efficiency, times waking up after sleep onset, and total sleep.

To standardize dietary intake and blood glucose levels, participants will be asked to record their dietary intake for the 24 h before each condition in a standardized food diary and closely match their diet for each pre-condition day. They will also be asked to fast and abstain from caffeine after dinner the night before. Additionally, participants will wear a continuous blood glucose monitor (Abbott FreeStyle Libre sensor) during the 24 h before, and during each experimental condition.

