### Experimental Conditions

To minimize physical activity the morning of the visit participants will be transported to the laboratory *via* taxi. On the morning of testing, participants will be asked to provide four saliva samples (for cortisol testing); immediately after waking and at 30, 45, and 60 min thereafter. Once they arrive at the laboratory, pre-condition outcome measures will be collected, followed by an individually standardized breakfast (consisting of maximum two slices of bread with butter and cheese, a bowl of yogurt, a banana, and a glass of water), with no specific time restriction for eating. Participants at their initial visit will be advised to eat their preferred amount, which will be subsequently weighed and recorded. The portion sizes will be then replicated at each visit. The activPAL activity monitor and glucose monitor will be worn during the experimental conditions to monitor sitting time during the test day.

The three experimental conditions (summarized in Figure 1) are: (A) uninterrupted sitting for 3 h with a 3-min social break every 30 min (SOCIAL); (B) sitting for 3 h with a 3-min bout of moderate-intensity walking on a treadmill every 30 min (WALK), or (C) sitting for 3 h with a 3-min bout of simple resistance activities every 30 min (SRA). During the sitting, participants will be permitted to read a book and drink water, but not use any technological devices or doze off. The SOCIAL break (condition A) will consist of a 3-min chat between the research staff and the participant. The WALK break (condition B) will be performed at moderate intensity (75–80% of maximal heart rate), normalized to individual participants’ VO_2max_ (see Supplementary Material). For the SRA break (condition C), participants will be asked to complete 20-s bodyweight half-squats, 20-s calf raises, and 20-s gluteal contractions and knee raises repeated three times in sequential order by following standardized video instructions (as per Dempsey et al., 2017). At 135 min after the experimental condition commences, participants will be offered a toilet break.

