### Outcome Measures

Outcome measures will be collected immediately before and immediately after each experimental condition.

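### Within-condition pre-to-post change is assigned to the primary question and underlies hypotheses (b) and (f), but it runs from a fasted pre-test to a fed post-test, so only the time-by-condition contrasts can support a conclusion about breaks

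*Protocol article*

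**What the plan says.** All references are to the protocol article.

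- **Primary question (Introduction).** It asks "what are the acute (immediate) effects of uninterrupted sitting and frequent, short activity breaks during 3 h of sitting on cerebral blood flow". It therefore covers sitting as well as breaks.
- **Analysis (Data Analysis).** The sentence that opens with the primary research question says that linear mixed models "will be used to assess within condition differences in the changes in cerebral blood flow (oxy-Hb) between pre- and post-tests". The Benjamini–Hochberg correction over channels is attached to that sentence. The next sentence reads: "Time and condition interactions will be used to estimate differences between conditions".
- **Hypotheses (Introduction).** Hypothesis (a) is between conditions: the change "will be greater following the conditions with frequent, short activity breaks compared with the uninterrupted sitting condition". Hypothesis (b) is within conditions: "Cerebral blood flow will be greater post-intervention compared to pre-intervention for the frequent, short activity breaks conditions, but not for the uninterrupted sitting condition". Hypothesis (f) has the same form for arterial stiffness: a fall from pre-test after the break conditions and no change after sitting.
- **Prandial state (Pre-experimental Day Monitoring).** "They will also be asked to fast and abstain from caffeine after dinner the night before".
- **Order of events (Experimental Conditions).** On arrival, "pre-condition outcome measures will be collected, followed by an individually standardized breakfast", with no time limit for eating. The Figure 1 caption places the conditions after breakfast.
- **Stated timing (Outcome Measures).** "Outcome measures will be collected immediately before and immediately after each experimental condition".
- **Arterial stiffness (Arterial Stiffness).** The 5 min of supine rest before the recordings takes place at pre-test only.

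**The concern.** Randomising the order of conditions protects comparisons between conditions. It does not protect a comparison of pre-test with post-test inside one condition, because everything else that differs between those two moments is confounded with the condition. Here the differences are an overnight fast against a recent meal, at least 3 h of elapsed morning, and a repeat of the n-back. For the augmentation index there is also a change in the resting procedure.

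Two consequences follow.

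1. A shift due to meal, time or retesting could be reported as an effect of the breaks, or of sitting. Half of the primary question concerns uninterrupted sitting, yet all three conditions consist of 3 h of sitting and SOCIAL is the reference. Nothing in the design separates the effect of sitting from the other things that happen between the two tests.
2. Hypotheses (b) and (f) describe change after breaks and none after SOCIAL. Observing the first and failing to detect the second does not test whether the conditions differ, and with 13 participants a non-significant SOCIAL result is weak evidence of no change.

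**Working it through.** **Plan's own figure.** The Sample Size section gives effect sizes of 0.9 to 2.4, a two-tailed test at 0.05, a value of 0.8 (labelled β, read here as power) and a largest requirement of 13. A paired t-test with the noncentral t gives power 0.810 at n = 12 and 0.845 at n = 13 for a standardised effect of 0.9. An effect of 0.85, which rounds to 0.9, needs exactly 13. The target reproduces and is not in dispute; n = 13 is used below.

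**Step 1: sequence of a test day, identical in all conditions.** Fast after dinner → arrival → pre-test → breakfast, untimed → 3-h condition → post-test. The pre-test is fasted, the post-test is fed, and they lie at least 3 h apart. The pre-test comes immediately before breakfast, not immediately before the condition, so the Outcome Measures sentence conflicts with Experimental Conditions.

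**Step 2: what each contrast estimates.** Write the expected change in condition c as s + e(c), where s is the shift shared by all visits (meal, elapsed time, retesting) and e(c) is the effect of the condition.

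- Within condition: s + e(c). The two parts cannot be separated.
- WALK minus SOCIAL: [s + e(WALK)] − [s + e(SOCIAL)] = e(WALK) − e(SOCIAL). The shift cancels. The same holds for SRA minus SOCIAL.
- Sitting alone: e(SOCIAL) appears only as s + e(SOCIAL), or as the reference in a difference. It is not identified.

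**Step 3: chance of a significant within-condition change when no condition has any effect.** Inputs: n = 13, two-sided 0.05, e(c) = 0 for all c, and s in SDs of the change score. The documents give no value for s, so a range is assumed. The one-sample t has 12 degrees of freedom and noncentrality s√13.

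| Assumed shared shift (SD) | P(within-condition change significant) |
|---|---|
| 0 | 0.05 |
| 0.3 | 0.17 |
| 0.5 | 0.38 |
| 0.6 | 0.51 |
| 0.8 | 0.75 |
| 0.9 | 0.85 |

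In 20,000 simulated trials per setting, at shifts of 0 to 0.8 SD, the WALK-minus-SOCIAL contrast of changes was significant 0.049 to 0.051 of the time.

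**Step 4: the pattern of at least one break condition significant and SOCIAL not.** If the three tests were independent with common probability p, the pattern has probability [1 − (1 − p)²](1 − p).

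- s = 0.6, p = 0.51: [1 − 0.49²] × 0.49 = 0.7599 × 0.49 = 0.37.
- s = 0.9, p = 0.845: [1 − 0.155²] × 0.155 = 0.976 × 0.155 = 0.15.

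The same 13 people supply all three changes, so independence is a simplification. By simulation with a correlation of 0.5 between changes, the figures are about 26% (0.6 SD) and 12% to 13% (0.9 SD). At a correlation of 0.7 they are about 20% and 10%. The fair comparator, at least one of the two direct contrasts significantly favouring breaks, is about 4.5%. If both break conditions must rise while SOCIAL does not, the pattern is rarer: about 9% and 7% at a correlation of 0.5.

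**The case against.** The strongest reply is that the valid analysis is already in the plan. The sentence after the within-condition one provides time-by-condition interactions, and the models for the secondary outcomes also cover differences between conditions. Hypotheses (a), (c) and (d) are already worded against sitting. Breakfast portions are replicated at each visit, and nothing links eating time to condition. This stands. A reader might infer that the primary question is answered only from within-condition change, or that the trial cannot estimate the effect of breaks. The document supports neither reading, because an additive shared shift cancels in the interaction.

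A reader might also infer that (b) and (f) will be decided by significance after breaks and non-significance after SOCIAL. The document states no such rule. The wording of the two hypotheses only invites it, and how they are weighed against (a) may be settled in an analysis plan that is not shown.

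There are partial safeguards. The primary outcome is the oxy-Hb difference between 1-back and 2- or 3-back, so a uniform shift in oxy-Hb level cancels. A meal or time effect on the response to task load does not. Short-separation channels deal with superficial blood flow. Practice at familiarization and on each test day reduces learning effects but does not show that they are absent.

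Finally, the shift sizes are assumptions. The value of 0.9 equals the lower end of the exercise effects in the Sample Size section; it is not an estimate of a meal effect. That limits the size of the problem that can be claimed, but not the confounding itself.

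**Conclusion.** The point holds for within-condition results. The article assigns to the primary question a contrast that mixes the condition with a change from fasted to fed, at least 3 h of elapsed time and retesting. Hypotheses (b) and (f) rest on contrasts of that kind, and for (f) the supine rest at pre-test only is a further difference. Within-condition change cannot be attributed to breaks or to sitting. With no non-sitting condition, the absolute effect of uninterrupted sitting cannot be estimated by any term in the model.

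The comparison of breaks with SOCIAL is sound, provided the shared shift is additive and common to the three conditions; hypothesis (a) is validly tested by the planned interaction.

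The size is illustrative. With shared shifts of 0.3 to 0.9 SD and no condition effect, within-condition tests are significant about 17% to 85% of the time, against about 5% for the direct contrast. The break-but-not-SOCIAL pattern is about 26% at 0.6 SD and 12% to 13% at 0.9 SD with a correlation of 0.5, or 37% and 15% under independence. The true shift may be smaller, and the documents do not allow it to be estimated.

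**What to change.** 1. In Data Analysis, name the time-by-condition contrasts WALK versus SOCIAL and SRA versus SOCIAL as the confirmatory analysis of the primary question.
2. Restate hypotheses (b) and (f) as differences in pre-to-post change versus SOCIAL.
3. Report within-condition changes as descriptive estimates with confidence intervals, noting that they include meal, elapsed time and retesting and, for the augmentation index, the rest at pre-test only.
4. State that the trial does not estimate the absolute effect of uninterrupted sitting, and word the primary question and the conclusions to match.
5. Reconcile the timing in Outcome Measures with Experimental Conditions by saying that pre-test measures are taken fasted, before breakfast.

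The cost is wording and test hierarchy only. The model, the data collected and the number of participants stay as they are.
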